**Figure 3 figure3:**
[figure not shown]
Transverse plane ultrasound image of the prostate. Fibres (circles) positioned in both transition zones while maintaining a safe distance from the urethra (triangle), rectum and prostatic capsule.

**Table 1 table1:** Overview of the number of fibers used and fiber distance based on prostate volume (based on the manufacturer’s instructions).

Prostate volume (cc)	Power (watts)	Energy per fiber (J)	Number of fibers per lobe	Fiber distance (mm)	Number of pullbacks	Total delivered energy (J)
30-40^a^	3	1800	1	—^b^	0	3600
	3	1800	1	—	1	7200
40-80^a^	3	1800	1	—	1	7200
	3	1800	2	10-15	0	7200
	3	1800	2	10-15	1	14,400
>80^a^	3	1800	2	10-15	1	14,400
	3	1800	2	10-15	2	21,600

^a^The operator, based on the prostate shape and length, should determine the optimal fiber setup.

^b^Not applicable.

Following the procedure, the patient will be observed for several hours for spontaneous voiding without significant residual urine. If the patient does not have spontaneous voiding or has a residual volume of ≥500 mL, an indwelling catheter will be placed. For these cases, 10 to 14 days later, a trial without a catheter will follow.

### Contrast-Enhanced Ultrasound

Multiple CEUS investigations of the prostate will be performed over the course of this study. CEUS is used because the ablation zone is not visible on gray-scale ultrasound (Figure 4) [20]. The contrast agent is a gas-filled microbubble (Sonovue, Bracco). This contrast agent enables visualization of the vascular architecture of the prostate. Thus, nonvascularized coagulated areas are visible as hypo-intense (black) regions [21]. Several studies have used CEUS for laser ablation area visualization in prostate cancer.

**Figure 4 figure4:**
[figure not shown]
On the left the contract-enhanced ultrasound image of the prostate of the prostate 1 month following TPLA treatment, with dark areas corresponding with the treated areas. On the right the co-localized grey-scale image.

Lindner et al demonstrated that CEUS shows a clear hypo-intense zone, which corresponds with the ablated area following focal laser ablation of prostate cancer [21]. Patelli et al confirmed this result by demonstrating the applicability of CEUS for ablation zone determination following TPLA treatment [13]. CEUS is considered safe, because the lungs eliminate the contrast agent and ionizing radiation is not needed. A hypersensitivity allergic reaction to the contrast agent is a serious, but rare adverse event (<0.01%) [22].

CEUS imaging will be performed according to internal hospital protocol, with a Philips iU 22 machine interfaced with an end-firing transrectal probe (Philips Healthcare, Bothell). Prostate imaging consists of prostate volume measurement in 2 directions in B-mode (gray scale) setting. This will be followed by a transverse and sagittal sweep of the prostate in contrast mode, during peak inflow of the first bolus of 2.4 mL contrast agent. Subsequently, images will be made of the maximal diameter of both lesions in the sagittal and transverse planes. Treatment volumes will be calculated on the contrast images using an ellipsoid formula [23]. The second bolus will be used to capture contrast inflow and outflow within 1 plane over the course of 2 min.

### Follow-Up

Patients will undergo a strict follow-up. The patient will be called 3 to 5 days post-TPLA treatment to inquire about health status. The patient will visit the hospital 4 times following TPLA treatment at 4 weeks, 3 months, 6 months, and 12 months. During these visits, medical history, adverse events using the Clavien-Dindo classification, physical examination (on indication), and uroflowmetry will be performed. Patient-reported outcome measures (PROMs) (IPSS, IIEF-15, VAS, and HGS) are used to objectify functional outcomes, pain, and symptoms. Prostate imaging will comprise a CEUS +/– 2 hours following treatment, at 4 weeks and 12 months. CEUS is considered the only invasive procedure during follow-up. Follow-up is completed after 12 months.

### Data Analysis

Study population characteristics (eg, age, medical history, medication, peak urinary flow rate, prostate volume, and detrusor pressure) and procedural information (eg, fibers placed, energy delivered, procedural success, adverse events, and lesion volume) will be reported descriptively. Functional outcomes by peak urinary flow and PROMs will be tested using a Wilcoxon signed-rank test. Statistical tests will be performed two-sided, and *P*<.05 is considered significant. Statistical analysis will be performed using SPSS version 25.0 (SPSS Inc).

### Safety

The investigators will monitor patient safety. They can withdraw a patient from the study for medical reasons. In accordance to section 10, subsection 4, of the Wet Medisch-Wetenschappelijk Onderzoek met Mensen (medical research involving human subjects act in the Netherlands), the investigators will suspend the study if there is sufficient ground that continuation of the study will jeopardize patients’ health or safety. The investigators will notify the accredited institutional review board if this is the case. In case of an adverse event or serious adverse event, the responsible authorities will be informed.

### Benefits and Risks

All patients included in this study have LUTS and have an indication for prostate desobstruction. This study aims to treat patients for their LUTS by TPLA to evaluate safety and feasibility and functional outcomes. The benefits focus on the minimal invasive character of TPLA and subsequent day care setting without clinical admission. Spinal or general anesthesia is made redundant by use of local anesthesia and optional conscious sedation.

Risks for patients focus on the procedure, subsequent device-related adverse events, and unknown long-term functional outcomes of the treatment. Needles are used to introduce fibers into the prostate, possibly causing damage and perforation of surrounding structures (eg, neurovascular bundle, urethra, or rectal wall). As ultrasound guidance is being used, these events are unlikely to occur. Hemorrhage, infection, fistula formation, sepsis, and death can occur. However, risks are expected to be low because the transperineal approach is already applied for biopsies of the prostate and has proven to be safe [24]. Furthermore, Patelli et al reported no procedure-related adverse events in 18 patients [13]. Therefore, risks of adverse events are minimal as described earlier.

Nonetheless, TPLA is a relatively new technique and long-term outcomes are unknown. Patelli et al described short-term functional outcomes demonstrating that the peak urinary flow rate improved from 7.6 to 13.3 mL per second at 3 months post-TPLA. Yet, studies that applied other minimal invasive LUTS treatments showed a reduction of long-term effectiveness and increase of retreatment rates over time [8,9]. Thus, when feasibility of TPLA in patients that are candidates for surgical desobstruction can be demonstrated, future studies will be able to focus on the long-term outcomes.

## Results

Presently, patient recruitment is ongoing. Initial results on safety and feasibility are expected in early 2020. Follow-up outcomes following TPLA treatment are expected in late 2020. Outcomes will be published in peer-reviewed medical journals and presented at international conferences.

## Discussion

### Overview

TPLA is a technique that might efficiently treat BPO under local anesthesia in an outpatient setting. This pilot study will provide initial data on the safety and feasibility of TPLA treatment in healthy men eligible for standard surgery before launching large-scale comparative studies.

### Comparison With the Literature

The design of our study aims to show safety and feasibility in men fit for standard surgical treatment. The first TPLA pilot study by Patelli et al [13] showed promising results for men unfit for standard treatment. They treated 18 patients and showed technical safety and feasibility for men unfit for TURP due to comorbidities [13]. Functional outcomes showed peak urinary flow improvement from 7.6 (SD 2.7) to 13.3 (SD 76.2) mL per second at 3 months. IPSS improved from 21.9 (SD 6.2) to 10.7 (SD 4.7) at 3 months. Interestingly, a relatively long postoperative catheterization time of 17.3 (SD 10.0) days was observed. However, half of the study population already needed an indwelling catheter before TPLA treatment. Our study aims to study the safety and feasibility of TPLA treatment for men fit for standard treatment. Our study also aims to confirm the outcomes of previous studies, in a population with proven bladder outlet obstruction. Additionally, our study aims to preserve spontaneous voiding posttreatment by including men with spontaneous voiding before treatment. Nevertheless, risk for obstruction following treatment due to edema remains. Therefore, outcomes regarding spontaneous voiding post-treatment are evaluated after 10 patients have been treated. If more than 50% of treated patients do not spontaneously void, the subsequent 10 patients will receive a Foley catheter for 10 to 14 days.

### Transperineal Laser Ablation Versus Interstitial Laser Coagulation

Interestingly, TPLA is based on the technique of inducing coagulative tissue necrosis, which is similar to the tissue response found in transurethral ILC. However, the long-term outcomes of ILC appeared to be inferior to TURP [7]. As ILC and TPLA are based on a similar concept, it could cause criticism studying this approach. However, the currently available TPLA treatment has benefits when compared with the previous ILC treatment.

First, TPLA uses a transperineal approach in contrast to ILC which uses a transurethral fiber introduction. The transperineal approach of TPLA treatment aims to leave the urethra undamaged, hereby reducing post-treatment irritative voiding complaints when compared with the transurethral approach, which causes urothelial damage and subsequent irritative voiding complaints.

Second, the multifiber setup of TPLA treatment enables simultaneous treatment of both prostate lobes with 1 or 2 fibers each depending on prostate volume. If a median lobe is present, this can be treated as well. Additionally, each fiber can be configured individually, which enables shaping of the ablation zone. Hereby, a desired ablation volume is obtained faster when compared with serial treatment with 1 fiber used with ILC. Thus, the unique multifiber approach is expected to increase ablation volume faster and subsequently improved outcomes, especially in larger prostates.

Finally, TPLA is performed under continuous ultrasound imaging guidance, which provides visualization of the complete gland. This leads to improved treatment planning and ablation zone shaping, and subsequently theoretically improved outcomes.

### Study Limitations

Nonetheless, this pilot study has several limitations. First, inclusion is set at 20 patients and is considered sufficient for determining safety and feasibility. However, this is not sufficient for measuring functional outcomes, as the study is not powered for this. Thus, successive studies are necessary once this study shows initial beneficial results. In addition to this, we have initiated an international registry to collect data from other centers that apply TPLA for BPO (ClinicalTrial.gov registration: NCT03776006). Second, a learning curve might be expected in the number of fibers placed and their location. Therefore, only a limited number of physicians will perform the TPLA procedures for this pilot.

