### Aim

The aim of this study is to prove safety and feasibility of TPLA treatment for men with BPO eligible for standard surgical treatment.

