### Outcomes

Feasibility is measured by technically successfully (without device-related adverse events) performed TPLA procedures. If 90% (18/20) of the treatments are successfully performed, we conclude that the treatment is feasible. Safety is assessed by the adverse events using the CTCAE version 5.0. TPLA is defined to be safe when ≤10% (2/20) of the patients experience adverse events of grade 3 or higher. For the secondary objectives, the functional outcomes are measured by uroflowmetry and International Prostate Symptom Score (IPSS) and erectile function by International Index of Erectile Function 15 (IIEF-15).

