Overall, 20 patients will be included in this study. This number is based on the IDEAL stage 2a recommendations for surgical innovations and past pilot studies [13-15].

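### Twenty patients and the 2/20 and 18/20 cuts can screen for a poor result, but at conventional confidence they cannot prove safety or feasibility as the article claims

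*Protocol article*

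**What the plan says.** Under Aim, the protocol article states: "The aim of this study is to prove safety and feasibility of TPLA treatment for men with BPO eligible for standard surgical treatment".

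Outcomes turns this into two rules on raw counts. For safety: "TPLA is defined to be safe when ≤10% (2/20) of the patients experience adverse events of grade 3 or higher". For feasibility: "If 90% (18/20) of the treatments are successfully performed, we conclude that the treatment is feasible".

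Population and Sample Size sets the number at 20 and gives the reason: "This number is based on the IDEAL stage 2a recommendations for surgical innovations and past pilot studies". It states no precision, error rate or assumed true rate.

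Study Limitations then says that "inclusion is set at 20 patients and is considered sufficient for determining safety and feasibility". The next sentence concedes a lack of power, but for the functional outcomes only.

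Under Data Analysis, procedural success and adverse events are to be reported descriptively. The only significance level in the article is two-sided 5%, given with the Wilcoxon tests of functional outcomes.

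**The concern.** Safety and feasibility are the primary objectives. The article claims that the trial will prove them and that 20 men are enough to determine them. The rules behind those words look only at the observed proportion, and in 20 men an observed proportion is compatible with a wide range of true rates.

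Followed as written, the plan turns 2 events in 20 into an unqualified verdict of safe, although the data would not exclude a true rate about three times the tolerated one. The Discussion presents the results as the step before large comparative studies and as an essential basis for future treatment, so the strength of the verdict matters. The limitation that bears most on the primary objectives is acknowledged only for the secondary ones.

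**Working it through.** **Inputs.** n = 20, single arm (Population and Sample Size). Safe if X ≤ 2, where X is the number of men with a grade 3 or higher event (Outcomes). Feasible if S ≥ 18, where S is the number of successful treatments; the article writes 18/20, read here as at least 18 and one treatment per man (Outcomes).

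**The plan's own figures.** 2/20 = 10% and 18/20 = 90%, so the cuts are arithmetically right. The choice of 20 cannot be reproduced, because no precision, power or assumed rate is given.

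**Step 1: best case for safety, 0/20.** At a true rate of 10%, the chance of no event is 0.9^20 = 0.122. The exact upper limit solves (1 − p)^20 = α:
- one-sided 95%: 1 − 0.05^(1/20) = 13.9%
- two-sided 95%: 1 − 0.025^(1/20) = 16.8%

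Both exceed 10%.

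**Step 2: best case for feasibility, 20/20.** The lower limit is 0.05^(1/20) = 86.1% (one-sided) or 0.025^(1/20) = 83.2% (two-sided). Both are below 90%.

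**Step 3: the other results that pass.** Exact (Clopper-Pearson) upper limits for the event rate come from the beta quantile with parameters x + 1 and 20 − x:

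| Events in 20 | One-sided 95% upper | Two-sided 95% upper |
|---|---|---|
| 0 | 13.9% | 16.8% |
| 1 | 21.6% | 24.9% |
| 2 | 28.3% | 31.7% |

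The full two-sided 95% interval is 1.2% to 31.7% for 2/20 events and, as its mirror image, 68.3% to 98.8% for 18/20 successes.

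**Step 4: how often the rule says safe.** P(X ≤ 2) = (1 − p)^20 + 20p(1 − p)^19 + 190p²(1 − p)^18. At p = 0.10 this is 0.122 + 0.270 + 0.285 = 0.677.

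| True grade 3+ rate | P(declared safe) |
|---|---|
| 5% | 0.925 |
| 10% | 0.677 |
| 15% | 0.405 |
| 20% | 0.206 |
| 25% | 0.091 |
| 30% | 0.035 |

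The feasibility rule behaves the same way, with failures in place of events: 0.677 at a true success rate of 90% and 0.206 at 80%.

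**Step 5: does the interval method matter?** For 0/20 at two-sided 95%, the upper limit is 16.8% exact, 16.1% Wilson and 11.7% Jeffreys; all exceed 10%. Of the one-sided variants tried, two fall below 10%: Jeffreys at 95% (9.0%) and Wilson at 90% (7.6%). The exact one-sided 90% limit is 10.9%. With the exact method, 0/20 excludes 10% only at one-sided confidence of about 1 − 0.122 = 87.8% or lower.

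**Step 6: scale.** For the exact upper limit to fall below 10% with zero events, n must be at least 29 (one-sided 95%) or 36 (two-sided 95%). With two events it must be at least 61 or 70.

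**The case against.** The strongest reply is that this applies a test the plan never set. Outcomes defines safe by an observed count and nowhere promises to exclude a 10% true rate. The article calls the study a pilot at IDEAL stage 2a, ties the number to that stage, and says in the Discussion that it will give initial data before comparative studies. As a screen the rule is useful: it rejects a true rate of 20% in 79% of trials (1 − 0.206), 25% in 91% and 30% in 96.5%. A statistical analysis plan may also supply intervals.

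Most of this stands. It defends the sample size and the cuts, and a missing interval alone would be no finding. It does not defend the claims to prove safety and to have enough patients to determine it. Those claims are printed in the article and conflict with its pilot framing; an interval reported elsewhere would not correct them.

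A reader might infer more than the documents support:
- **That 20 is the wrong number.** Nothing in the article shows this for a stage 2a pilot.
- **That the rule concerns serious events.** The endpoint is CTCAE grade 3 or higher, which grades severity.
- **That the two pass probabilities can be multiplied to give the chance of passing both.** Success is defined as freedom from device-related adverse events, so one event can count against both rules and independence cannot be assumed.
- **That the remark in Benefits and Risks, "Therefore, risks of adverse events are minimal as described earlier", is refuted by setting its 18 event-free patients against the 10% limit.** Those patients were unfit for standard surgery and the count was of procedure-related events, so both population and endpoint differ. The section also relies on ultrasound guidance and on experience with transperineal biopsy.

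**Conclusion.** The concern holds as a fault in what the article claims, not in its size or its cuts. At 95% confidence by exact methods, one-sided or two-sided, no result in 20 men shows an event rate below 10% or a success rate above 90%. A procedure with a true rate of 20%, twice the tolerated one, would be called safe about one time in five.

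This rests on conventional confidence levels, independent patients, all 20 men being treated and counted, and the feasibility rule meaning at least 18. At lower confidence, or with the two less conservative one-sided methods shown above, 0/20 would just exclude 10%; results of 1/20 or 2/20 would not under any method tried.

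Severity is moderate. The plan can be run as designed, but its primary conclusion would be stated more firmly than the data allow.

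**What to change.** Keep 20 patients and both cuts, and make four changes to the text.

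1. In Outcomes, present 2/20 and 18/20 as pilot screening criteria for whether to go on to further study, not as definitions of safe and feasible.
2. In Data Analysis, state that both proportions will be reported with exact (Clopper-Pearson) 95% confidence intervals alongside the verdict.
3. In Aim, replace the verb prove with: obtain a preliminary estimate of safety and feasibility, and screen for an unacceptable rate. Use the same wording in Study Limitations in place of the claim that 20 is sufficient.
4. In Study Limitations, extend the acknowledged limitation from functional outcomes to safety and feasibility. Note, for example, that even 0/20 events leaves an exact upper limit of 13.9% (one-sided 95%) or 16.8% (two-sided 95%).

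The cost is wording and two intervals, with no extra patients and no change to procedures. The downside is that the stated conclusion becomes less favourable.

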### Conclusion

In conclusion, TPLA treatment offers a unique multifiber and transperineal approach for the treatment of LUTS due to BPO under local anesthesia resulting in ablation zone shaping and creation of an ablation zone volume in a short period of time. We hypothesize that this study will confirm safety and feasibility of TPLA treatment of men with LUTS due to BPO and fit for standard surgery. The results of this study will broaden the knowledge on TPLA treatment in men with LUTS and are expected to be an essential basis for future BPO treatment using this approach.

## Abbreviations

BPO: benign prostatic obstruction
CEUS: contrast-enhanced ultrasound
HGS: Hematuria Grading Scale
IIEF: International Index of Erectile Function
ILC: interstitial laser coagulation
IPSS: International Prostate Symptom Score
LUTS: lower urinary tract symptoms
PROM: patient-reported outcome measure
TPLA: soracteLite transperineal laser ablation
TURP: transurethral resection of the prostate
VAS: visual analogue scale
